## Objective

2

To evaluate the efficacy of oral vitamin D supplementation in the reduction of the body mass index (BMI) and the lipid profile in adolescents and young adults of the SIMBA cohort in Bucaramanga, Colombia.

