## Methods

3

Design: Two-arm, triple-blind, parallel randomized controlled clinical trial.

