### Statistical analysis

3.11

An analysis will be made by intention to treat. The description of the categorical variables will be made by means of absolute and relative values. Quantitative variables that present a normal distribution in Shapiro Wilk's test will be reported as mean and standard deviation, otherwise the median and interquartile range will be presented. The comparison of the basal characteristics of the study groups (intervention and control) will be done using the ratio comparison test (Chi-square or Fischer's exact test) and the Student's t-test or Mann-Whitney's U-test.

Quantitative outcome variables will be contrasted through paired t-tests or Wilcoxon tests for quantitative variables, methods of longitudinal data analysis will also be explored and for categorical ones the Mc Nemar test will be used. Statistical significance will be considered for all hypothesis tests when the *P* value is less than .05.

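### Section 3.11 specifies no between-arm analysis for any outcome: it gives the outcomes paired tests and McNemar, and keeps the two-sample tests for baseline characteristics

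*Protocol article*

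**What the plan says.** Section 3 (Methods) of the protocol article gives the design as "Two-arm, triple-blind, parallel randomized controlled clinical trial". The Objective is "To evaluate the efficacy of oral vitamin D supplementation in the reduction of the body mass index (BMI) and the lipid profile". The sample size in section 3.3 rests on a 20% difference between the intervention and control groups.

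Section 3.11 (Statistical analysis) sets out the tests:

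- Baseline: "The comparison of the basal characteristics of the study groups (intervention and control) will be done using the ratio comparison test" (chi-square or Fisher's exact), with Student's t or Mann-Whitney for quantitative variables.
- Quantitative outcomes: "Quantitative outcome variables will be contrasted through paired t-tests or Wilcoxon tests for quantitative variables".
- Categorical outcomes: "for categorical ones the Mc Nemar test will be used".
- In addition: "methods of longitudinal data analysis will also be explored", with no model, group term or contrast named.
- Analysis set: "An analysis will be made by intention to treat".
- Threshold: "Statistical significance will be considered for all hypothesis tests when the *P* value is less than .05".

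Outcomes are measured at baseline, before allocation, and once more at 15 weeks (sections 3.5 and 3.7).

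**The concern.** A paired test needs matched observations. The arms contain different people, so the only pairing in this design is a participant's baseline with the same participant's week-15 value. The tests named for the outcomes therefore ask whether values changed over time. They do not ask whether 1000 IU changed them more than 200 IU did. The tests that can compare two independent groups are assigned to baseline characteristics, where any difference after proper randomisation is due to chance.

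Several things could move both arms together: season, taking part in a study with diet and activity assessments, and the 200 IU that controls receive. The last matters most for 25(OH)D, which is a primary outcome. A before-after test cannot separate such a change from an effect of the higher dose. Nor does significance in one arm and not in the other test a difference between arms. The Discussion says that positive results would make it possible to recommend supplementation, so the analysis behind that statement needs to compare the arms.

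**Working it through.** **1. Tests set against the design**

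| Use in section 3.11 | Test named | Can it compare 1000 IU with 200 IU? |
|---|---|---|
| Baseline characteristics | Chi-square, Fisher, Student's t, Mann-Whitney | Yes, but applied to baseline only |
| Quantitative outcomes | Paired t or Wilcoxon | No, before versus after |
| Categorical outcomes | McNemar | No, before versus after |
| To be explored | Longitudinal methods | Possibly, but no arm contrast is stated |

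The article does not say which Wilcoxon test is meant. It is offered as the alternative to the paired t-test, and the same section calls the two-sample rank test Mann-Whitney's U, so the signed-rank test is the natural reading.

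**2. The sample-size figure**

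The only related figure in the article is the 270 participants of section 3.3. No control-group rate is given, so it can be matched only under an assumed one. For 20% versus 40%, two-sided 5%, 90% power:

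n = [1.96·√(2·0.3·0.7) + 1.2816·√(0.2·0.8 + 0.4·0.6)]² / 0.2² = (1.270 + 0.811)² / 0.04 ≈ 109 per arm.

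Allowing for 20% loss, 109/0.8 ≈ 137 per arm, or 274 in total, close to 270. Other assumed rates (lower rate 5% to 60%) give about 156 to 350 in total. The figure is attainable but cannot be confirmed. What matters here is that the stated target is a difference between two independent groups, and the outcome tests in section 3.11 do not estimate one.

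**3. How often a shared change would mislead**

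Assumptions, none of them stated in the article: paired t-tests run in each arm; two-sided 5%; normal changes; no true arm difference; a shared mean change of δ standard deviations (SD) of the change score; 60 evaluable per arm (75 less one fifth), with 75 per arm as a check.

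- Probability p that one arm is significant: noncentral t with n − 1 degrees of freedom and noncentrality δ√n.
- Exactly one arm significant: 2p(1 − p).
- Only the 1000 IU arm significant: p(1 − p).

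With n = 60 and δ = 0.25, the noncentrality is 0.25 × √60 = 1.936 and the critical value 2.001, so p = 0.478. Then 2 × 0.478 × 0.522 = 0.499 and 0.478 × 0.522 = 0.250.

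| δ (SD) | p, n = 60 | Exactly one arm | Only 1000 IU arm |
|---|---|---|---|
| 0 | 0.050 | 9.5% | 4.8% |
| 0.1 | 0.119 | 21% | 10% |
| 0.2 | 0.332 | 44% | 22% |
| 0.25 | 0.478 | 50% | 25% |
| 0.3 | 0.628 | 47% | 23% |
| 0.4 | 0.862 | 24% | 12% |
| 0.5 | 0.968 | 6% | 3% |

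At δ = 0.5 one-arm-only results become rare because both arms are nearly always significant. The 1000 IU arm is then significant in about 97% of trials although the dose difference does nothing.

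With 75 per arm and δ = 0.25, p = 0.570, exactly one arm is significant in 49% and only the 1000 IU arm in about 25%. The result hardly depends on whether 60 or 75 are evaluable.

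In 20,000 simulated trials at δ = 0.25, a two-sample t-test on the changes was significant in about 5% (4.9% with 60 per arm, 4.8% with 75).

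**The case against.** **The longitudinal clause could cover it.** With two arms and two time points, a longitudinal model could contain a group-by-time term. This stands in part. A reader might infer that the arms will never be compared, and the article does not support that. It does support the narrower statement that no arm comparison of outcomes is specified: the clause is exploratory and names no contrast.

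**The article does not say that the tests are run within each arm.** True; they could be pooled over arms. The one-arm-only rates above assume per-arm testing. The defect does not depend on it, because a pooled before-after test does not compare the arms either.

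**An article condenses, and a fuller plan may supply the comparison.** That would answer a complaint about missing detail. Here the article positively assigns paired tests to the outcomes and two-sample tests to baseline, so a fuller plan with a between-arm analysis would conflict with this text.

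**It is a pilot.** Section 3.11 still applies a 5% threshold to every hypothesis test, and the Discussion looks ahead to a recommendation and to health policy.

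Three further inferences are tempting but unsupported:

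- Regression to the mean as a source of shared change. The eligibility criteria select nobody on BMI, lipid, glucose or 25(OH)D values, and the 150 are drawn at random from the list.
- That 20% loss is expected in this trial. The 20% is an allowance in the 270-participant calculation; none is stated for the 150.
- That intention to treat requires a baseline-constrained longitudinal model here. With complete baselines, one follow-up and a common covariance, that model gives the same arm estimate as ANCOVA on those with a week-15 value, so it adds no protection. Handling of missing values may in any case be left to the analysis plan.

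**Conclusion.** The point holds as a defect in what section 3.11 states. It specifies no between-arm analysis for any outcome, and the tests it names belong to a before-after question that matches neither the parallel design, nor the efficacy objective, nor the basis of the sample size. This must be corrected before analysis.

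The error rates show how far before-after results can mislead if they are read as evidence for 1000 IU. They do not predict what the investigators will report, since the article gives no rule for interpreting the paired tests. They rest on per-arm testing, an assumed number evaluable and an assumed shared change. The conclusion that paired tests cannot compare the arms needs none of these assumptions.

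**What to change.** Replace the outcome sentence in section 3.11 with text to this effect:

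- For each quantitative outcome, the analysis is the difference between arms at week 15 (1000 IU minus 200 IU) with a 95% confidence interval, from an analysis of covariance on arm and the baseline value of that outcome, with participants analysed in the arm to which they were randomised.
- For any categorical version of an outcome, a between-arm comparison adjusted for baseline status replaces McNemar.
- Within-arm changes are reported as description only.
- If longitudinal methods are kept, the arm contrast that they estimate is named.

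The cost is one paragraph of wording. Baseline and week-15 values are already collected, so no new data, visits or participants are needed.

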### Sample size

3.3

The simple size was calculated considering the following parameters: an expected difference in the study outcomes (overweight, obesity, and alteration of the lipid profile) of 20% between the intervention group and the control group; a power of 90%, an alfa of 5%, an intervention group/control group ratio of 1:1, and a 20% adjustment for losses to follow-up, resulting in a sample of 270 participants (n = 135 intervention and n = 135 control group). The OpenEpi software was used for the calculation. Since this is a pilot study and considering the feasibility, the research team decided on a sample size of 150 participants (n = 75 intervention group and n = 75 control group).

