### Outcomes

3.9

*Primary outcome:* These are biochemical and anthropometric measurements that allow to respond to the purpose of the study. These include:

Total BMI. This requires taking the size in meters (m) and weight in kilograms (kg).Lipid profile: Measurements will be made of the serum levels of total cholesterol, low-density lipoprotein (LDL), high-density lipoprotein (HDL), and triglycerides.Serum levels of 25(OH) D.

*Secondary outcomes:* These are complementary measurements for the primary outcomes.

Waist-hip ratio: determines the intra-abdominal fat levels and is obtained by dividing the waist perimeter by the hip perimeter.Skin folds: These are taken for the indirect estimation of body fat percentage by means of measuring the bicipital, tricipital, abdominal, and subscapular folds.Fasting glycemia.

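### BMI and the lipid profile can each be called significant by more than one analysis route at P<.05, and the plan names no route as the deciding one

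*Protocol article*

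**What the plan says.** Three sections of the protocol article bear on this.

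- **3.3 Sample size.** The calculation rests on "an expected difference in the study outcomes (overweight, obesity, and alteration of the lipid profile) of 20" per cent between arms, with "a power of 90%, an alfa of 5%, an intervention group/control group ratio of 1:1". These are categories, compared as proportions.
- **3.9 Outcomes.** The primary outcomes are measured values: BMI, serum 25(OH)D and, for lipids, "Measurements will be made of the serum levels of total cholesterol, low-density lipoprotein (LDL), high-density lipoprotein (HDL), and triglycerides". No categorical outcome is defined here.
- **3.11 Statistical analysis.** "Quantitative outcome variables will be contrasted through paired t-tests or Wilcoxon tests for quantitative variables"; then "methods of longitudinal data analysis will also be explored and for categorical ones the Mc Nemar test will be used". The section closes with "Statistical significance will be considered for all hypothesis tests when the *P* value is less than .05".

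No section says whether the measured or the categorical form of BMI or lipids decides, or how a longitudinal result ranks beside the simple tests.

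**The concern.** The issue is several analyses of the same outcome, which is distinct from the number of outcomes. BMI appears as a value in 3.9 and as overweight and obesity in 3.3. Lipids appear as four levels in 3.9 and as one category, alteration of the profile, in 3.3. Section 3.11 supplies a test for each form and leaves room for unspecified longitudinal models, and all are judged at the same threshold.

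Two things follow. The chance that at least one route reaches P<.05 when nothing is happening can exceed the stated 5% within a single outcome. And when one route is significant and another is not, the plan has no rule for which is the trial's answer. This has consequences because the Discussion says that positive results would make it possible to recommend supplementation for BMI and lipids.

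**Working it through.** **Inputs from the protocol.** 75 per arm and 20% losses (3.3), so 75 × (1 − 0.20) = 60 evaluable per arm; measurements at baseline and week 15 (3.7); threshold .05 for every test (3.11).

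**Assumed, because the protocol gives neither.** Baseline-to-week-15 correlation between 0.5 and 0.95; proportion above the cut-off between 18% and 50%; normal data.

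**Step 1: the plan's own figure.** The control rate is not stated. Taking 40% v 20%, two-sided 5% and 90% power:

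n = [1.960·√(2·0.30·0.70) + 1.282·√(0.40·0.60 + 0.20·0.80)]² / 0.20² = (1.270 + 0.811)² / 0.04 ≈ 108.2 per arm.

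108.2 / 0.80 ≈ 135, the stated number per arm. Other rates also come close (35% v 15% with continuity correction gives 134), so the match is not unique. It does show that 270 is consistent with a comparison of proportions, that is, of categories. No error in 270 is claimed.

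**Step 2: reference values for independent tests.** Chance of at least one P<.05 under no effect = 1 − 0.95^k. For k = 2 this is 9.75%; for k = 3 it is 14.3%. Tests on the same data are correlated, so lower values are generally expected.

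**Step 3: simulation under no effect, 60 per arm, one outcome.** Within-arm rows refer to tests in one arm.

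| Routes combined | Any P<.05 |
|---|---|
| Paired t + exact McNemar | 5.3–7.1% |
| Paired t + asymptotic McNemar | 8.3–9.2% |
| Baseline-adjusted between-arm test + one chi-square, continuity-corrected | 7.1–8.1% |
| Same, uncorrected (correlation 0.5–0.9) | 8.2–9.5% |
| Paired t + exact McNemar + one longitudinal contrast | 8.6–10.3% |
| Paired t + asymptotic McNemar + one longitudinal contrast | 11.4–12.4% |
| Same, with two longitudinal contrasts | 12.5–13.6% |
| Baseline-adjusted + change score + one chi-square, corrected | 9.0–9.4% |
| Same, uncorrected | 10.1–11.3% |
| BMI: baseline-adjusted + change score + two cut-offs, corrected | 11.0–11.1% |
| Same, uncorrected | 13.3–14.3% |

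Two routes therefore give roughly 5–9.5%. Settings that pair uncorrected chi-square with a change-score test, or with the baseline-adjusted test at correlation 0.95, reach 10.0–10.1%. Three routes give roughly 8.5–14%. The four-test BMI case is about 10–14%, rounded outward.

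**Step 4: disagreement between routes.** Here disagreement means significant versus not significant.

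- Under no effect, paired t and asymptotic McNemar disagree in 7–9% of trials.
- With an assumed within-arm shift of 0.15 SD, they disagree in about 20–78%.
- With an assumed between-arm shift of 0.3 SD, the continuous and single-cut-off tests disagree in 31%, 44% and 72% of trials at correlations 0.5, 0.7 and 0.9. Power is 46%, 62% and 96% for the continuous test and about 24–25% for the categorical one.

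Both tests significant in opposite directions occurred in about 0.01% of null trials or fewer.

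**Step 5: one deciding test.** The paired t-test alone gave 4.8–5.2%, so naming one analysis brings the risk for that outcome back to about 5%.

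**The case against.** The strongest reply is that double testing is inferred. Section 3.11 assigns tests by variable type, section 3.9 lists only measured values, and nowhere is BMI or any lipid said to be analysed in both forms. This stands in part: a reader might infer that the plan requires every outcome to be tested several ways, and it does not. It permits it. The permission comes from stated text, since 3.3 calls the categories the study outcomes and 3.11 provides a test for categorical outcomes.

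A reader might also infer that each of the four lipids is tested as a level and again as altered or not. Section 3.3 names a single lipid category, so this is unsupported, and the two-cut-off figure applies to BMI only.

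The wording that longitudinal methods will be explored suggests exploratory intent. That is fair, and without them the two-route range applies. But the significance sentence exempts nothing.

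The figures depend on the tests chosen, and this stands. Exact McNemar or a continuity correction lowers them, so 8% is not a floor. In the other direction, counting within-arm tests in both arms gives 16–19%, but that excess arises from within-arm testing, a separate problem.

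Finally, ranking primary and supportive analyses is commonly left to a statistical analysis plan. Silence alone would be no finding. Here the article itself states the outcomes in two forms and applies one significance rule to all tests; a later plan would have to override that text.

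**Conclusion.** The point holds as a matter of what the plan allows. BMI, and the lipid profile as a whole, can be called significant by more than one route, and no route is named as deciding. With no true effect and 60 per arm, the false-positive risk for one outcome ranges from barely above 5% (two routes, exact McNemar) to about 14% (three routes, or BMI with both cut-offs and four between-arm tests). The correlations, prevalences and normality behind these figures are assumptions.

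It would go too far to say that every outcome carries 8–14%, or that the plan yields opposite answers. The routes can disagree only in the sense of significant versus not significant, and how often depends on an effect size that the protocol does not give. For 25(OH)D, section 3.3 names no categorical form, so the duplication there is limited to the longitudinal methods. Calling the study a pilot does not remove the point, since the Objective is stated as efficacy.

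**What to change.** In section 3.11, name one deciding analysis per primary outcome: the between-arm difference in the continuous week-15 value as defined in section 3.9, adjusted for its baseline value, two-sided 5%, with a 95% CI. Analyse skewed variables such as triglycerides on the log scale.

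State that categorical versions (overweight, obesity, altered lipid profile), rank tests and other longitudinal models are supportive, reported with estimates and CIs. Limit the P<.05 significance sentence to the deciding analyses. Align the outcome wording of section 3.3 with section 3.9.

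This takes a few sentences before unblinding and needs no new data or participants; the baseline values are already collected. The price is that a finding seen only in a categorical or alternative model cannot be claimed as positive. Multiplicity across the primary outcomes is a separate matter that this change does not address.

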### Ethics approval and consent to participate

3.12

The research will be carried out following the principles established in the Good Clinical Practice in Clinical Trials GPC/ICH. It is considered a minimum risk study according to resolution 008430 of October 4, 1993 of the Colombian Ministry of Health, since it includes the administration of a commonly used vitamin supplement with a wide therapeutic margin and for its administration the indications, doses and routes of administration established by the Institute for Drug and Food Surveillance (Invima, acronym in Spanish) are considered. The vitamin supplement is supplied by the laboratory Farma de Colombia, commercially known as Farma D, whose presentation is in soft gelatin capsules and with registration number 2017 M-0012231-R1.

The processing of personal and clinical data and biological samples will be handled according to the Habeas Data Act (Act 1266 of 2008) of the government of Colombia.

The study was reviewed and endorsed by the Technical Scientific Committee (CTC) of *Fundacion Cardiovascular de Colombia* (FCV) according to minute N°133 of May 2018 and has the approval of the Research Ethics Committee (IEC) of the FCV according to minute N°480 of July 16, 2019.

The study nurse will explain the objectives, importance, risks, benefits of the research and the confidentiality of the data. Written informed consent will be given to study participants and for participants under the age of 18 we will obtain from a parent or guardian.

## Discussion

4

The role of vitamin D as a protector against cardiovascular disease is widely recognized.^[2,3]^ For consideration, vitamin D supplementation is being widely studied to determine its effect on the control of cardiovascular risk factors and metabolic syndrome, including obesity, dyslipidemia, and impaired blood glucose.^[5]^

Studies on the effect of supplementation in adolescents and young adults are scarce; however, the favorable effect of supplementation in the serum levels of 25 (OH) D in school-age children with VDD and the reduction in blood pressure, the concentration of fasting glucose, and improvements in sensitivity to insulin in children with overweight and obesity is widely known.^[14,15]^ Notwithstanding this, more clinical trials are required to confirm these findings.

This research is innovative considering that there are few studies on adolescent and young adult populations and that these have not been carried out in Latin America.^[14,15]^ Consequently, if this trial provides positive results, it will be possible to recommend oral vitamin D supplementation for the reduction of BMI and lipid profile in the studied population. In addition, it is a low-cost and easy-to-apply intervention that could contribute to the formulation and implementation of health policies.
